## Abstract

**Background:**

Cognitive and mood disorders negatively impact daily life in patients with multiple sclerosis (MS). Pharmacological treatments did not demonstrate any effect on cognition compared with cognitive rehabilitation (CR). However, if CR programs offer promising results on cognition, they are less consistent concerning mood and quality of life (QoL). In this context, we designed a randomized controlled trial to evaluate the efficacy of an innovative computerized CR program, conducted at home, on QoL. Secondary objectives will estimate the improvement, or the stabilization over time, of patients’ cognitive performances and their emotional affects.

**Methods:**

Forty MS patients (relapsing-remitting or secondary progressive forms) who have cognitive impairment will be recruited for the trial (called SEPIA-NCT03471338) and randomly assigned to either the experimental group or the control group. Patients randomly assigned in the experimental group will perform a home-based CR program with psychological support during eight consecutive weeks. CR will be based on computerized cognitive exercises from the PRESCO® software developed by HAPPYneuron^©^. Training sessions (three sessions of 45 min per week) will consist of short exercises evaluating a broad range of cognitive domains and will be personalized for each patient (tracking tool and supervised guidance). The control group, designed to control for non-specific elements of the intervention, will receive only psychological support consisting of various issues related to MS, such as everyday cognitive-related difficulties or management of emotions. QoL, assessed by the MUSIQOL (Multiple Sclerosis International Quality Of Life) questionnaire, will be evaluated three times (at baseline and after 1 week and 25 weeks after home-based intervention) as well as secondary outcomes measuring self-esteem, cognition, depression, anxiety, metacognition, fatigue, and sleep quality. Given the expected MUSIQOL variation, the inclusion of 20 patients per group (alpha risk 5% and power 80%) will be required.

**Discussion:**

Evidence suggests that computerized programs may be a practice option for CR for people with MS, but there is a paucity of studies evaluating QoL. We hope that this innovative program will highlight such benefits over time in patients’ daily life. In the future, such programs will allow a wider range of available therapeutic options for MS patients with cognitive impairment and for practitioners in charge of their care.

**Trial registration:**

ClinicalTrials.gov identifier: NCT03471338. Retrospectively registered on 25 April 2018. https://clinicaltrials.gov/ct2/show/NCT03471338?term=NCT03471338&cond=Multiple+Sclerosis&draw=2&rank=1.

## Background

The existence of cognitive disorders in multiple sclerosis (MS) has been widely studied over the last 20 years [1, 2]. These disorders may be considered the first predictive factor of high occupational disability rates [3] and have significant consequences for social, familial, and professional life (e.g., difficulties in meeting the demands of a job, resulting in dismissal, reclassification, or unemployment [3]).

Objective cognitive disorders, detected through traditional neuropsychological assessments, correlate weakly with cognitive complaints reported by patients [4]. In addition, current cognitive assessments do not capture real-world consequences of these deficits as reported by the patients [2]. The current challenge therefore is to find and offer effective alternatives to help patients managing their cognitive problems in daily life [3]. Cognitive rehabilitation (CR) may represent an alternative approach as it does not imply adverse side effects compared with pharmacological interventions [5].

Computer-assisted techniques are among the CR evidence-based practice options for health professionals, supplying a range of benefits [6]. They offer self-paced, individualized training providing new and challenging exercises [3, 7]. The level of difficulty of the task can be changed on the basis of the patient’s baseline skills and can be gradually adjusted as performance improves. They allow a feasible, simple, and friendly activity that requires less face-to-face intervention of health professionals in charge of CR [3, 5]. Stuifbergen et al. conducted an at-home computer-based CR trial in order to help patients with MS to achieve the highest level of cognitive functioning and functional independence [3]. The authors showed that the intervention group outperformed the control group on all measures, including a better personal efficiency, more frequent use of compensatory strategies, and improved performance in neuropsychological tests [3]. In addition, Messinis et al. reported improved verbal and visuospatial episodic memory, information processing speed, and executive functioning after an intervention of 20 individualized 1-hour sessions over a 10-week period using RehaCom® (HASOMED GmbH, Magdeburg, Germany) software in relapsing-remitting (RR) MS patients with mild to moderate cognitive disorders [8]. A systematic review identified a paucity of studies, including activities of daily living as secondary outcomes, among other criteria, with promising results [6].

However, as evidenced by two recent Cochrane reviews [9, 10] and a systematic literature review of 33 studies [11], the efficacy of rehabilitation techniques remains weak and inconclusive. In fact, most of them involved methodological flaws such as time of intervention, goals, frequency of sessions, and content as well as underlying theoretical bases. Further work is required to demonstrate the potential long-term effect of CR. Better outcome measurements and related ecological validity are also warranted. Finally, rehabilitation studies have used two main approaches: those aimed at increasing cognitive performance [6] and those that adopt a holistic approach [12], aiming to improve quality of life (QoL). Although most studies emphasize the need to consider QoL, they sparsely consider this field as a primary outcome. Similar conclusions can be drawn for other concepts such as self-esteem.

Despite these promising results, no computer-assisted rehabilitation trial has focused on improving QoL or mood disorders to date. Most studies aimed to improve cognitive functioning through increased performance during neuropsychological testing. However, these assessments are lacking ecological sensitivity, and potential improvements include more than a cognitive score but rather cover various aspects of our psychic functioning. According to this overview, qualitative, more holistic approaches must be conducted to better evaluate the effect of CR on patient self-perception. Previously, we had a first experience on 10 MS patients with cognitive impairment during an open non-controlled trial using a similar CR home-based program. This pilot study (unpublished) showed that patients get some clinical benefit (based on self-perception questionnaire) in their QoL.

Therefore, we designed this trial in order to compare the effect of an innovative home-based program of computerized CR with psychological support versus a control psychological intervention on QoL in MS patients presenting cognitive impairment. In addition, we will estimate the improvement or stabilization over time of self-esteem, cognitive performance, emotional affect (depression and anxiety), metacognition, fatigue, and sleep quality as secondary measure outcomes which represent important issues for clinical care of patients with MS.

## Methods

### Design

This study is a randomized controlled trial with three data collection points (Fig. 1): baseline (week 0), short-term retest (week 10) one week after the end of the home-based intervention (8 consecutive weeks), and long-term retest at week 34. The trial was registered in ClinicalTrials.gov registry as NCT03471338. A Standard Protocol Items: Recommendations for Interventional Trials (SPIRIT) checklist is provided in Additional file 1.

**Fig. 1 Fig1:**
[figure not shown]
Flowchart of the trial design. *Abbreviation*: *CR* cognitive rehabilitation. ^1^Number of planned patients to recruit

### Site and participant recruitment

The trial will be monocentric and conducted at the MS Expert Centre, Department of Neurology, Caen University Hospital, Normandy, France. The CR program (cognitive exercises and psychological support) will be performed at patients’ homes in Western Normandy.

Volunteers will be identified during routine care in the outpatient clinic of the MS Expert Centre. Verbal and written detailed information about the ongoing study will be provided to the patient in a standardized way by using a specific informed consent form that has been validated by the ethics committee. Recruitment will take place over the course of 30 months.

### Ethical approval

This trial was registered under “Minimal risk and constraint interventional research” in accordance with the terms of article L.1121–1 of the French Public Health Code (act number 2012–300 of March 5, 2012, and its implementing decree number 2016–1537 of November 16, 2016). Ethical approval was granted by the French Regional Ethics Committee “CPP Nord Ouest II” on September 7, 2017 (ID RCB 2017-A017 36–47).

### Participants

To be eligible for participation, subjects must meet the following defined inclusion criteria:
confirmed diagnosis of MS in accordance with the 2010 revised McDonald criteria [13]RR or secondary progressive (SP) phenotypes of the diseasebe male or female between 18 and 65 years of agedisease duration of not more than 25 yearsExpanded Disability Status Scale score (EDSS) of not more than 5.5clinically inactive phase of the disease as defined by the new Lublin criteria [14]impaired cognitive performance at least 1.65 standard deviations below normative data at one test of the BCcogSEP battery [15]French native speakingcomputer with Internet access holderlegal capacity to consent to the trial (via written informed consent).

Exclusion criteria will be as follows:
other neurological, psychiatric, or developmental diseases prior to MS diagnosishead injury sequelaechronic alcohol or drug consumptionEDSS score of at least 6presence of relapse or treatment with corticosteroids at least 1 month before recruitment (or both)patient under wardshipcognitive assessment within the last 6 months (particularly including all or some of the tests proposed in the present trial)presence of dementia in accordance with the criteria of the fifth edition of the *Diagnostic and Statistical Manual of Mental Disorders* (DSM V) [16] or sufficient cognitive impairment that may interfere with cognitive assessment or the administration of CR exercises (or both)any visual or motor deficit that may prevent cognitive assessments or CR exercise administration (or both).

#### Exclusion procedure

Intercurrent disease diagnosed during follow-up, occurrence of relapses (whether or not treated with corticosteroids), patient’s decision or investigator’s decision (or both) for any reason will result in withdrawal of the assigned treatment. However, outcome data will be collected on those patients and included in the intention-to-treat analysis.

### Outcome measurements

For an overview of outcome assessment timelines, see Table 1.

**Table 1 Tab1:** Schedule of assessments

		Study period												
		Screening	Baseline	Home-based intervention									Short-term follow-up	Long-term follow-up
Visits (weeks)		W-1	W0	W1	W2	W3	W4	W5	W6	W7	W8	W9	W10	W34
Informed consent		X												
Eligibility screen		X												
Randomization		X												
Neuropsychological assessment 1	Cognitive complaint questionnaire	X												
	BCcogSEP	X												
	VAPS	X												
	Multiple errands test	X												
Neuropsychological assessment 2	MUSIQOL		X										X	X
	SEI		X										X	X
	MADRS		X										X	X
	HAMA		X										X	X
	BICAMS = SDMT, CVLT-II, BVMT-R		X										X	X
	MCQ-30		X										X	X
	EMIF-SEP		X										X	X
	PSQI		X										X	X
Active control group	At-home set-up			X										
	Phone follow-up				X	X	X		X	X	X	X		
	At-home follow-up							X						
Experimental group with CR intervention	CR intervention				X	X	X	X	X	X	X	X		
	At-home set-up			X										
	Phone follow-up				X	X	X		X	X	X	X		
	At-home follow-up							X						

*Abbreviations*: *BCcogSEP* Batterie Courte d’évaluation des fonctions cognitives destinées aux patients souffrant de Sclérose En Plaques (French brief test battery evaluating cognitive functions in multiple sclerosis), *BICAMS* Brief International Cognitive Assessment for Multiple Sclerosis, *BVMT-R* Brief Visuospatial Memory Test – Revised, *CR* Cognitive rehabilitation, *CVLT* California Verbal Learning Test, *EMIF-SEP* Echelle Modifiée d’Impact de la Fatigue dans la Sclérose En Plaques (modified fatigue impact scale – multiple sclerosis), *HAMA* HAMilton Anxiety rating scale, *MADRS* Montgomery and Åsberg Depression Rating Scale, *MCQ-30* MetaCognition Questionnaire-30, *MUSIQOL* MUltiple Sclerosis International Quality Of Life, *PSQI* Pittsburgh Sleep Quality Index, *SDMT* Symbol Digit Modalities Test, *SEI* Self Esteem Inventory, *VAPS* Virtual Action Planning Supermarket

#### Primary outcome

The primary outcome is QoL, measured by the global score of the Multiple Sclerosis International Quality Of Life (MUSIQOL) questionnaire [17]. The MUSIQOL is a validated multi-dimensional 31-item self-report questionnaire encompassing the following nine dimensions: activity of daily living, psychological well-being, symptoms, relationships with friends and relationships with family, satisfaction with health care, sentimental and sexual life, coping, and rejection. Each item is scored on a scale ranging from 1 to 5; higher scores are suggestive of higher QoL. This questionnaire shows satisfactory psychometric properties (external validity, internal consistency, reliability, reproducibility, and acceptability), even in patients with cognitive dysfunction [18, 19]. This outcome will be evaluated during baseline and short- and long-term assessments to evaluate the immediate and long-term effect of cognitive rehabilitation, respectively.

#### Secondary outcomes

Secondary outcomes are listed as follows:
Self-esteem measured by the Self-Esteem Inventory (SEI) [20]. This is a 58-item self-report scale. Participants must answer by ticking the box “like me” or “not like me”. The SEI is divided into four subscales: general, social, family, and professional self-esteem. The higher the score from this scale, the greater the self-esteem.Depression measured by the Montgomery and Åsberg Depression Rating Scale (MADRS) [21]. This is a 10-item clinician-administered scale evaluating the intensity of various depression symptoms (from apparent sadness to suicidal thoughts).Anxiety measured by the Hamilton Anxiety rating scale (HAMA) [22]. The HAMA consists of 14 clinician-administered items, each defined by symptoms, and measures both psychic anxiety (mental agitation and psychological distress) and somatic anxiety (physical impairments). Each item is scored on a scale ranging from 0 to 4; higher scores are suggestive of higher anxiety.Metacognition measured by the MetaCognitions Questionnaire (MCQ-30) [23]. The MCQ-30 is a short and easy-to-use self-reported questionnaire for multi-dimensional measure of metacognitive factors (beliefs, metacognitive judgements, and monitoring process).Fatigue measured by the “Echelle Modifiée d’Impact de la Fatigue dans la Sclérose En Plaques” (EMIF-SEP) (modified fatigue impact scale in multiple sclerosis [24]). This scale consists of 40 items evaluating various aspects of fatigue (cognitive, physical, and psychosocial fatigue dimensions). Each item is scored on a scale ranging from 0 (completely false) to 4 (completely true). The higher the score, the greater the fatigue.Subjective sleep quality measured by the Pittsburgh Sleep Quality Inventory (PSQI) [25]. This is a self-rated questionnaire which assesses sleep quality and disturbances across 19 items generating seven “component” scores: subjective sleep quality, sleep latency, sleep duration, habitual sleep efficiency, sleep disturbances, use of sleeping medication, and daytime dysfunction. The PSQI score yields a diagnostic sensitivity and specificity in distinguishing good from poor sleepers.Objective cognitive disorders measured by the Brief International Cognitive Assessment for Multiple Sclerosis battery (BICAMS), proposed as a brief tool for evaluating and screening cognitive disorders for neurologists, currently validated in French [26]. It consists of the Brief Visuospatial Memory Test – Revised (BVMT-R) measuring visual memory [27], the California Verbal Learning Test (CVLT) measuring verbal memory [28], and the Symbol Digit Modalities Test (SDMT) measuring information processing speed [29].

All of these outcomes will also be evaluated at all three time points: baseline (week 0), short-term retest (week 10) one week after the end of the home-based intervention, and long-term retest at week 34.

### Initial screening assessment

#### Informed consent

Before recruitment, patients will be informed about the aim, benefits, constraints, and risks of the trial. A detailed information letter and a consent form will be provided by investigators. All of the assessments at screening, baseline, and short-term and long-term visits will be conducted at the MS Expert Centre, Department of Neurology, Caen University Hospital.

#### Screening assessment

After patients have provided informed written consent, the screening visit (about 2 h) will be performed. The investigating neurologist will check inclusion and exclusion criteria mentioned above for eligibility. Then participants will undergo a neuropsychological assessment including the following:
a cognitive complaint questionnairethe BCcogSEP cognitive battery (frequently used and well-validated French battery in MS derived from the Rao’s Brief Repeatable Battery of neuropsychological tests) [15, 30]the multiple errands test (executive functional test evaluating planning functions) [31]the Virtual Action Planning Supermarket (VAPS) test (virtual reality counterpart of the multiple errands test) [32]

Considering the patient’s MS clinical features and evidence of cognitive impairment from the BCcogSEP assessment, investigating neurologists and neuropsychologists will decide whether the patient is eligible or ineligible. Finally, eligible patients will be randomly assigned in the trial in accordance with the following procedure.

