### Sample size and data analysis

Based on previous research [34], the standard deviation of the MUSIQOL scores was estimated at 16 points, and the correlation coefficient between scores at baseline and short-term follow-up at 0.85. We hypothesized an average increase of 3 points in the MUSIQOL scores at short-term follow-up for the active control group (a low effect size, equal to about 0.2) and an average increase of 11 points for the experimental group (0.7 effect size), leading to an 8-point difference between the two groups. Given a bilateral alpha error of 5% and a power of 80%, a minimal sample size of 18 patients per group is needed to compare the mean scores of the two groups at short-term follow-up, adjusting for the baseline scores [35]. To account for potential drop-outs, 20 patients will be included in each group.

The mean MUSIQOL scores at short-term follow-up will be compared between the two groups (CR intervention and active control) by using an analysis of covariance (ANCOVA), adjusting for the baseline MUSIQOL scores. The same type of analysis will be conducted at long-term follow-up and for secondary outcomes. An intention-to-treat analysis will be carried out as the primary analysis [36]. The results of a complementary per-protocol analysis will also be presented, as recommended by several authors [37, 38]. Significance level will be fixed at a *P* value of less than 0.05. Statistical analyses will be performed by using IBM SPSS software (IBM, Armonk, NY, USA) [39].

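### As worded, the relapse/corticosteroid exclusion bars events a month or more old and misses those in the last month, contradicting the relapsing-remitting and inactive-phase inclusions

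*Protocol article*

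**What the plan says.** All references are to the protocol article.

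- **Participants, inclusion list.** Patients may have the relapsing-remitting (RR) or secondary progressive form, must be in an inactive phase under a cited clinical definition, and may have had the disease for up to 25 years.
- **Participants, exclusion list.** A patient is excluded for a relapse, a corticosteroid treatment, or both, where the timing is given as *at least* one month before recruitment. No upper limit is set on how far back the event may lie.
- **Screening assessment.** The list is the operative rule: "The investigating neurologist will check inclusion and exclusion criteria mentioned above for eligibility". The section does not restate the window. It adds that neurologists and neuropsychologists decide eligibility from the clinical features and the cognitive battery.
- **Exclusion procedure.** After entry, the events that end the assigned treatment include "occurrence of relapses (whether or not treated with corticosteroids"). This concerns follow-up and sets no entry window.
- **Trial status.** Sixteen patients had been randomised and recruitment was continuing.

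**The concern.** The exclusion appears to run in the opposite direction from the criteria around it. Someone following it exactly would turn away a patient with a relapse two years ago and would not, on this line, turn away one who had a steroid course ten days ago. The inclusion list asks for RR patients who are currently inactive, which describes the first of these patients.

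Two things are at stake. First, eligibility cannot be audited against the published text: a monitor would have to flag most correctly recruited RR patients, or else ignore the line. Second, this is the only eligibility criterion that mentions corticosteroids, so if it misses recent courses, nothing else explicitly catches them. Baseline falls one week (± 7 days) after screening, that is 0 to 14 days later, so a course given shortly before recruitment could lie close to the baseline MUSIQOL. The article does not say how much that would matter.

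**Working it through.** **Step 1: the plan's own figure.** The only computed figure is the sample size, and it does not depend on the exclusion. The inputs, all from Sample size and data analysis, are "the standard deviation of the MUSIQOL scores was estimated at 16 points", "the correlation coefficient between scores at baseline and short-term follow-up at 0.85", "leading to an 8-point difference between the two groups", and "Given a bilateral alpha error of 5% and a power of 80"%.

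- Residual SD after baseline adjustment: 16 × √(1 − 0.85²) = 16 × √0.2775 = 8.43.
- n per group = 2 × (1.960 + 0.842)² × 8.43² / 8² ≈ 17.4, rounded up to 18, as stated.
- Power by normal approximation is 81% at 18 per group and 85% at 20 per group.

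No term in this formula involves the entry window, so correcting the window changes none of these numbers.

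**Step 2: the line read literally.** Let t be the months from the event to recruitment. As worded, the patient is excluded if t ≥ 1.

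| t (months) | As worded (t ≥ 1) | Opposite direction (t < 1) |
|---|---|---|
| 0.25, 0.5, 0.99 | not excluded | excluded |
| 1, 2, 6, 12, 60 | excluded | not excluded |

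The two readings disagree at every value of t. With no look-back limit and disease duration of up to 25 years, the literal rule can reach back over the whole disease history.

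**Step 3: does *at least* mean ≥ elsewhere in the list?** Yes. The disability exclusion uses it for an EDSS of 6 or more, and the cognitive inclusion uses it for 1.65 SD or more below the norm. When the list wants a recent window, for a previous cognitive assessment, it uses different wording that counts back over the last six months. So *at least* is not how this list otherwise expresses a recent window.

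**Step 4: set against the inclusions.** Under the literal rule, an RR patient passes only if no relapse or steroid course lies a month or more back. Any known relapse would then have to fall within the last month, and the inactive-phase criterion may reject that same patient. The two rules together leave little room for the RR group that the trial sets out to enrol. This is an internal contradiction.

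**Step 5: is it corrected elsewhere?** No. Screening assessment only points back to the list, Exclusion procedure deals with follow-up, and no other section gives an entry window for relapse or corticosteroids.

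**The case against.** The best defence is that the meaning can be recovered. The phrase can be taken as a minimum look-back, covering at least the month before recruitment, and on that reading nothing conflicts. The literal reading also defeats itself, since RR recruitment would largely fail and this would be noticed at once. In addition, the text is an article condensing a fuller protocol that is not shown, and the site may be working from correct wording there. Most of this stands, and it is why the point is a wording error and not evidence of wrong enrolment. It does not make the published line right: the charitable reading goes against the list's own use of *at least*, and no other section supplies the correct window.

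Several stronger conclusions are tempting, but the documents do not support them.

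- **That recently relapsed patients are being let in.** This exclusion alone would not stop them, but the inactive-phase inclusion and the clinicians' eligibility decision can.
- **That the sample size is undermined.** A reader might argue that unstable baselines would lower the assumed correlation of 0.85. Nothing in the article links this criterion to that correlation, so any lower value would be invented.
- **That the per-protocol set would lose most RR patients.** The article says only "The results of a complementary per-protocol analysis will also be presented". It does not define that population, may properly leave the definition to another document, and makes intention-to-treat primary.
- **That the comparison is biased.** Both groups pass the same screen before randomisation, and no difference between groups is shown.
- **That the 16 randomised patients were wrongly screened.** The article gives no evidence of this.

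**Conclusion.** The point holds as an internal contradiction in an operative eligibility rule. Followed exactly, the line excludes relapses and steroid courses one month or more old, without limit, and does not exclude those in the last month. That conflicts with enrolling RR patients in an inactive phase.

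In size it is modest. No sample-size or error-rate figure changes. The number of patients affected cannot be derived from the article. Allowing for the inactive-phase criterion, the gap that remains is mainly recent corticosteroid treatment in a patient otherwise judged inactive.

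The conclusion rests on reading *at least* as it is used elsewhere in the list, and on the article's text being the rule in force. If the full protocol words the window differently, the fault is confined to the publication. A drafting or translation slip is the likeliest explanation. Which window is clinically right is not for this review to say.

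**What to change.** The sponsor should:

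1. Reconcile the relapse/corticosteroid exclusion with the RR and inactive-phase inclusions, and confirm which direction the window is meant to run.
2. Restate the line unambiguously as an explicit period relative to recruitment, so that it says plainly whether events inside or outside that period exclude.
3. Confirm from the screening records that the 16 patients already randomised were assessed against that wording, and use it for the remaining 24 of the planned 40 (40 − 16 = 24).

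The cost is one reworded criterion, by amendment if the full protocol carries the same text or by correction of the article if it does not, plus a check of 16 records. The analysis and the sample size stay as they are.

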### Randomization and blinding

Eligible participants will be randomly assigned to one of two groups (experimental group with CR intervention or control group without CR intervention) via a computer-generated random number table in a 1:1 ratio by an independent trial-blinded statistician.

Patient, neurologist, and neuropsychologist in charge of CR intervention and psychological support for the control group will be not blinded due to the randomization procedure. The neuropsychologist in charge of clinical scales and cognitive evaluation for screening, baseline, and short- or long-term visits will be blinded.

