### Baseline assessment

All participants will undergo a baseline assessment (duration of about 1.5 h) one week (± 7 days) after the initial screening assessment.

Baseline will be conducted by an expert psychologist and will encompass the administration of the following clinical scales and self-report questionnaires:
MUSIQOL, which was the primary outcome measureSEIMADRSHAMAMCQ-30EMIF-SEP (modified fatigue impact scale in multiple sclerosis)PSQI

Neuropsychological assessment will be performed by using the BICAMS battery consisting of the BVMT-R, the CVLT, and the SDMT.

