#### Active control group

The word “active” refers to the fact that it was not ethically possible to randomly assign patients in this group without any psychological care as some patients may be disappointed by the result of the randomization. Participants will receive only psychological support in home visits or weekly phone calls. Psychological support will consist of clinical interviews about various issues related to MS, such as identity changes, everyday cognitive-related difficulties, management of emotions, promotion of coping strategies, theoretical information about MS-related symptoms, and promotion of metacognitive awareness or cognitive strengths or both. Note that participants in the control group will be given the opportunity to have the CR program as a priority after the end of their participation.

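### Randomisation is placed at the W-1 screening visit, before the W0 MUSIQOL, so the covariate of the primary ANCOVA is post-randomisation and open to influence by knowledge of allocation

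*Protocol article*

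**What the plan says.** Two places in the protocol article fix the time of randomisation, and they agree. The section Screening assessment ends the screening visit with "Finally, eligible patients will be randomly assigned in the trial in accordance with the following procedure". The randomisation row of Table 1 ("Randomization X") has a single mark, under W-1.

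The section Baseline assessment then states: "All participants will undergo a baseline assessment (duration of about 1.5 h) one week (± 7 days) after the initial screening assessment". MUSIQOL, the other scales and BICAMS are first collected at that W0 visit; Table 1 shows none of them at W-1. With the window as written, W0 falls 0 to 14 days after screening. Home-based intervention starts one week after W0 (section Group allocation).

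On who knows the arm, Randomization and blinding says: "Patient, neurologist, and neuropsychologist in charge of CR intervention and psychological support for the control group will be not blinded due to the randomization procedure". Only the neuropsychologist doing the assessments is blinded. The section Primary outcome describes the instrument: "The MUSIQOL is a validated multi-dimensional 31-item self-report questionnaire". The section Active control group justifies psychological support for controls on the ground that "some patients may be disappointed by the result of the randomization".

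The section Sample size and data analysis makes the W0 MUSIQOL the covariate of the primary ANCOVA and assumes a correlation of 0.85 with the short-term score. Nowhere does the article say when patients are told their arm, or that they are told only after W0.

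**The concern.** ANCOVA on a baseline score gives an unbiased treatment effect because randomisation cannot have influenced that score. This holds automatically when the score is taken before allocation. Here it is taken afterwards, from unblinded patients, on a self-report scale whose dimensions include psychological well-being, coping and rejection. A patient who knows the arm at W0 may score lower from disappointment or higher from hope. The arms would then differ at W0 because of allocation, and the model would treat that difference as chance imbalance and adjust the treatment effect for it. Blinding the assessor does not protect a self-completed score.

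The exposure matters because the sample size depends on this covariate. If the W0 score is in doubt, the unadjusted comparison at W10 has far too little power to replace the planned analysis.

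**Working it through.** **Inputs, all from Sample size and data analysis:** SD 16; correlation r = 0.85; target difference 11 − 3 = 8 points; two-sided alpha 5%; power 80%; 18 per group needed, 20 per group enrolled.

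**1. The plan's own figure.** Residual SD after adjustment = 16 × √(1 − 0.85²) = 8.43. Normal approximation: n = 2 × [8.43 × (1.960 + 0.842) / 8]² = 17.42, rounded up to 18 per group. The stated sample size is reproduced and is not in question.

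**2. Dependence on the covariate.** Without adjustment, n = 2 × [16 × (1.960 + 0.842) / 8]² = 62.8, so 63 per group. An unadjusted t-test for 8 points has 30.8% power at 18 per group and 33.8% at 20.

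**3. Bias per point.** With equal SDs at both visits the ANCOVA slope is r = 0.85. Let s be the W0 difference caused by allocation, with controls scoring lower by s.
- If the shift has vanished by W10, the W10 difference is still 8 and the estimate is 8 − 0.85s. The bias is −0.85 point per point.
- If the shift persists fully, the W10 difference is 8 + s and the estimate is 8 + s − 0.85s = 8 + 0.15s. The bias is +0.15 point per point.

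**4. Effect on power and error.** The documents give no value for s, so 1 to 3 points is an assumed range. The calculation uses the noncentral t distribution with 2n − 3 degrees of freedom and SE = 8.43 × √[(2/n) × (1 + 1/(2n − 4))], which is 2.853 at n = 18 and 2.702 at n = 20.

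| Transient shift s | Bias (0.85s) | Estimate if controls score lower | Power, n = 18 | Power, n = 20 | Two-sided type I error, n = 20, if the shift runs the other way |
|---|---|---|---|---|---|
| 0 | 0 | 8.00 | 77.7% | 82.2% | 5.0% |
| 1 | 0.85 | 7.15 | 68.2% | 73.1% | 6.1% |
| 2 | 1.70 | 6.30 | 57.3% | 62.2% | 9.4% |
| 3 | 2.55 | 5.45 | 45.8% | 50.2% | 15.1% |

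The first row lies slightly below 80% at n = 18 because the t distribution is used here and the normal approximation in step 1.

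If a 3-point shift persists fully, the estimate is 8 + 0.15 × 3 = 8.45, and power at 18 per group is about 82%. The harm therefore depends on how much of the shift has faded by W10.

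**5. Direction.** The only reaction that the article mentions is disappointment. In controls this would lower W0 scores and, if transient, bias the estimate against the intervention. The last column needs the opposite pattern, which the article does not suggest.

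**The case against.** The strongest reply is that a baseline taken after randomisation is not thereby a biased one. Patients must know their arm at W0, and the article does not say that they do. An independent statistician makes the allocation, the section Group allocation comes after Baseline assessment, and treatment starts a week after W0. Disclosure at or after W0 fits everything written, and a condensed article may leave that detail to the full protocol. This stands: the article fixes the order of events, not the time of disclosure. What remains is that the stated order creates the exposure and no stated safeguard closes it.

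Three stronger readings are tempting, and the documents do not support them.
- A reader might infer that the primary result is biased by 2.55 points, about a third of the 8-point target (2.55 / 8 = 32%). That takes 3 points as the reaction to allocation. The 3 points in the article are the assumed change in controls at short-term follow-up, after eight weeks of psychological support. They say nothing about one week's reaction to allocation. The figure also assumes that the shift vanishes completely by W10.
- A reader might infer a type I error of 15%. That requires both the 3-point shift and a direction opposite to the one that the article's remark on disappointment suggests.
- A reader might infer that patients who leave between W-1 and W0 are lost to the intention-to-treat analysis. How a missing baseline is handled belongs to an analysis plan that is not shown.

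Two further arguments add little. The blinded assessor meets patients who know their arm at W10 and W34 whatever the order. Low unadjusted power is common to any trial sized on ANCOVA; it matters here only because it removes the fallback.

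**Conclusion.** The point holds as a weakness in the stated sequence. Text and table both put randomisation before the first MUSIQOL, in unblinded patients, on a self-report scale, with a reaction to allocation foreseen. The primary covariate is therefore post-randomisation and unprotected as written.

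Whether bias has occurred, how large it is and which way it runs cannot be read from the documents. Under SD 16 and r = 0.85 the bias lies between −0.85 and +0.15 point for each point by which controls score lower at W0, depending on how far the shift persists to W10. For an assumed transient shift of 1 to 3 points against the intervention, power at 18 per group falls from 78% to between 68% and 46%. For the reverse direction, type I error at 20 per group would be between 6% and 15%. These figures are illustrations, not estimates.

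The sample size itself is correct. The point should be fixed because the remedy is cheap and no later analysis can recreate a baseline taken before randomisation. It does not make the trial uninterpretable.

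**What to change.** For all patients not yet randomised, move randomisation, both in Table 1 and in the last sentence of Screening assessment, to after completion of all W0 questionnaires and BICAMS and before the W1 home set-up. Failing that, state that allocation is withheld from the patient until the W0 assessments are complete.

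For patients already randomised, report the dates of randomisation, disclosure and baseline, and the W0 scores by arm. The article counts 16 randomised at the time of writing, which left 40 − 16 = 24; the number still open to change may be smaller. Treat any sensitivity analysis by order as descriptive, since groups of this size give little precision.

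Cost: a short amendment and two sequences within one trial. No visit, staff or patient is added, and the week between W0 and W1 still leaves time to arrange the home visits.
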